### Criteria for discontinuing or modifying the allocated interventions

During the study, those who experience dizziness, headache, motion sickness, or physical injuries that prevent their participation in this study will be excluded [13]. Participants may choose to discontinue their participation at any time for any reason.

### Provisions for post-trial care

This study investigates the efficacy and safety of the XR-based BLS training method. The probability of side effects during CPR training is very low. If any side effects occur during BLS training, appropriate treatment will be provided by each institution. In the case of serious side effects related to this study, the research director will follow each institution’s IRB protocol for reporting and subsequent measures required.

### Outcomes

#### Primary outcomes

The primary outcome will be the mean compression depth (mm) over 2 min, which will be measured in test #1, during which continuous chest compression will be delivered.

#### Secondary outcomes

The secondary outcomes will be as follows: the total number of chest compressions (*n*), the mean chest compression depth of each 30-s epoch, correct hand position (%), adequate compression depth (%), compression and full release (%), mean compression rate (number per minute), adequate compression rate (%), adequate compression depth and rate (%), and hands-off time (s).

In addition, the successful implementation of the steps involving checking for a response, calling for help, and checking for breathing will be compared. Other test results include the time interval from arrival on the scene (patient contact in the simulation) to the first chest compression (s), the total number of chest compressions with full release, correct hand position (total number of times), and correct AED use. For institutions where the policies allow recordings, the time interval from arrival on the scene (patient contact in the simulation) to the first chest compression (s), time from powering on the AED to defibrillation (s), and the time from checking for a response to defibrillation (s) will be assessed by reviewing the recordings (Tables 1 and 2). Regarding the questionnaire (Supplementary files #2, 3), a 5-point Likert scale will be used to assess the effectiveness of training and self-confidence in CPR after training (1 = strongly disagree, 5 = strongly agree) [17–19]. The demographics of the participants, such as age, sex, weight, height, and status of previous CPR training, will also be investigated (Table 3).

**Table 1 Tab1:** Test 1 results

Patients checking and calling for help						Valid value
Checking for response						Done/not done
Calling for help						Done/not done
Checking for breathing						Done/not done
**Chest compression**	Total	1st epoch	2nd epoch	3rd epoch	4th epoch	Valid value
*The time interval from arrival on the scene to the first chest compression (s)						0–60
Number of chest compressions (*n*)						0–400
Mean compression depth (mm)						1–100
Number of adequate compression depth (*n*)						0–400
Adequate compression depth (%)						0–100
Mean compression rate (*n*/min)						1–200
Adequate compression rate (%)						0–100
Adequate compression depth and rate (%)						0–100
Number of compressions with correct hand position (*n*)						0–400
Correct hand position (%)						0–100
Number of chest compressions with full release (*n*)						0–400
Compression and full release (%)						0–100
Hands-off time (s)						0–120
**AED**						Valid value
AED use						Done/not done
Correct AED use						Yes/no
*Time from powering on the AED to defibrillation (s)						0–120
*Time from checking for a response to defibrillation (s)						0–300

Epoch, 30-s epochs in test 1

Adequate compression depth, 5–6 cm; adequate compression rate, 100–120/min; correct hand position, hand position as the lower half of the sternum in the centre of the chest; compression and full release, less than or equal to 5-mm residual displacement; hands-off time, interruptions of chest compressions during cardiopulmonary resuscitation

*These variables can be obtained from recording devices such as smartphone cameras and video cameras

**Table 2 Tab2:** Test 2 results

Patients checking and calling for help						Valid value
Checking for response						Done/not done
Calling for help						Done/not done
Checking for breathing						Done/not done
Chest compression	1st cycle	2nd cycle	3rd cycle	4th cycle	5th cycle	Valid value
*The time interval from arrival on the scene to the first chest compression (s)						0–60
Number of chest compressions (*n*)						0–400
Mean compression depth (mm)						1–100
Number of adequate compression depth (*n*)						0–400
Adequate compression depth (%)						0–100
Mean compression rate (*n*/min)						1–200
Adequate compression rate (%)						0–100
Adequate compression depth and rate (%)						0–100
Number of compressions with correct hand position (*n*)						0–400
Correct hand position (%)						0–100
Number of chest compressions with full release (*n*)						0–400
Compression and full release (%)						0–100
Hands-off time (s)						0–120
AED						Valid value
AED use						Done/not done
Correct AED use						Yes/no
*Time from powering on the AED to defibrillation (s)						0–120
*Time from checking for a response to defibrillation (s)						0–300

Adequate compression depth, 5–6 cm; adequate compression rate, 100–120/min; correct hand position, hand position as the lower half of the sternum in the centre of the chest; compression and full release, less than or equal to 5-mm residual displacement; hands-off time, interruptions of chest compressions during cardiopulmonary resuscitation

*These variables can be obtained from recording devices such as smartphone cameras and video cameras

**Table 3 Tab3:** Demographics of participants

		Valid value
Age (years)		18–100
Sex		Male, female
Weight (kg)		40–150
Height (cm)		100–200
Previous CPR training		Yes/no

Previous CPR training: participants who have previously taken a CPR education

### Participant timeline

The participant timelines are presented in Fig. 4.

**Fig. 4 Fig4:**
[figure not shown]
The participant timelines. Test #1, hands-only CPR; Test #2, 5 cycles of 30 compressions and a 10-s rest

### Recruitment

Volunteers will be recruited through announcements published on the official website of each institution as well as via direct contact or email invitation. Participants will be enrolled competitively, but a minimum of 32 participants will be enrolled from each participating institution.

Regarding enrolment and allocation, once the participant informs the researcher of his or her intention to participate in the study through the website or email or directly to the researcher, the date will be coordinated with the researcher, and then informed consent will be obtained. After that, randomisation will be conducted. If there are not enough participants, the period will be extended to encourage voluntary participation.

Since this study is for nonhealthcare providers, nonhealthcare providers from each institution can all be potential participants. In case of significant delays in enrolment, we will visit the department where nonhealthcare providers work to inform them of the study objectives and encourage participation.

Furthermore, the possibility of self-selection bias exists, which causes those interested in CPR to participate in the study. However, considering that the primary outcome of this study is a comparison of chest compression depth between the two educational methods, self-selection bias may not cause significant bias in the interpretation of the results.

Recruitment will be completed once the required number of volunteers has been obtained. There will be no officially paid incentives to participate in this study, but small gifts may be provided depending on the institutional conditions.

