### Objectives

The aim of this study is to compare the efficacy of the XR-based basic life support (BLS) training method, which combines VR and the use of manikins, with that of the conventional training method. The hypothesis of this study is that the BLS skills gained by the XR method are not inferior to those gained by the conventional method.

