### Eligibility criteria

Individuals who are not healthcare providers and are 18 years old or older will be eligible for inclusion. Participants who are not capable of performing either the training or the CPR test due to physical or cognitive limitations will be excluded [7, 9–11]. Those who have upper extremity injuries or are pregnant will also be excluded [12]. If participants experience dizziness, headache, or motion sickness during the 2-min XR device adaptation period that prevents them from participating in the simulation study, they will also be excluded [13].

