## Assignment of interventions: allocation

### Sequence generation

Participants will be enrolled competitively, but a minimum of 32 participants will be enrolled from each participating institution to minimise racial and physical differences among the participants in each country. Random numbers will be generated with the stratified randomised permuted block design generated in the SAS software (version 9.4; SAS Institute Inc., Cary, NC, USA) by an independent statistician, and the randomisation sequence will be implemented in the Research Electronic Data Capture (REDCap) software (version 9.5.2, Vanderbilt University, Nashville, TN, USA). Institution and sex will be applied as the stratification factors, and REDCap will randomly allocate participants to the XR or conventional group.

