### Interim analyses

There are no planned interim analyses or subgroup or adjusted analyses in the trial.

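### Previously trained volunteers are admitted and no analysis by training history is planned, so a noninferiority result in the mixed sample may hide a deficit in untrained people

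*Protocol article*

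**What the plan says.** All references are to the protocol article.

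- **Objectives:** the hypothesis is that "the BLS skills gained by the XR method are not inferior to those gained by the conventional method".
- **Eligibility criteria:** "Individuals who are not healthcare providers and are 18 years old or older will be eligible for inclusion". The exclusions that follow do not mention earlier CPR training.
- **Secondary outcomes and Table 3:** the "status of previous CPR training, will also be investigated", as a yes/no item. The table footnote reads "Previous CPR training: participants who have previously taken a CPR education", with no limit on how recent or how thorough that education was.
- **Test procedure:** both tests come after the training. No compression test before training is described.
- **Recruitment:** the article grants that "the possibility of self-selection bias exists, which causes those interested in CPR to participate in the study", then concludes that "self-selection bias may not cause significant bias in the interpretation of the results", on the ground that the primary outcome is a comparison between the two methods.
- **Sequence generation:** "Institution and sex will be applied as the stratification factors". Previous training is not among them.
- **Interim analyses:** "There are no planned interim analyses or subgroup or adjusted analyses in the trial". Methods for additional analyses leaves room for unspecified later work on the data.

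**The concern.** The reassurance in Recruitment answers one question and leaves another open. Selection happens before randomisation, so prior skill is balanced between arms in expectation and does not confound the comparison. But prior skill can also change the size of the difference being compared. Someone who already compresses to adequate depth may score much the same after either method. The more such people are enrolled, the closer the mean difference is likely to lie to zero.

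In a superiority trial that costs power. In a noninferiority trial it moves the result towards the claim under test. The hypothesis is worded as skill gained, but with a post-training test only, skill gained cannot be separated from skill brought in. The one recorded item that could show whether the result differs by training history has no planned use. At stake is whether a positive result can be read as applying to people who have never been trained.

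**Working it through.** **Inputs from the article (Sample size; Statistical analysis of the primary and secondary outcomes).** Margin -5 mm, SD 10 mm, one-sided alpha 5%, power 90%, 69 per group before drop-out, 10% drop-out. Noninferiority is declared if the lower one-sided 95% limit is above -5 mm.

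**The plan's own figure.** n = 2 × 10² × (1.645 + 1.282)² / 5² = 68.5, so 69 per group; 69 / 0.9 = 76.7, so 77 per group and 154 in total. The stated size reproduces.

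**Decision threshold.** SE = 10 × √(2/69) = 1.70 mm. Noninferiority is declared when the estimate exceeds -5 + 1.645 × 1.70 = -2.20 mm.

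**Assumptions not in the article.** Let p be the previously trained share, and let f be the fraction of the untrained difference that trained people still show. Neither is given, so both are varied. The true difference in untrained people is set at the margin, -5 mm, and the SD is kept at 10 mm.

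Mixed-sample difference: d = -5(1 - p) - 5pf

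P(declare) = Φ((d + 5)/1.70 - 1.645)

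| p | d, f = 0 | P(declare) | d, f = 0.5 | P(declare) |
|---|---|---|---|---|
| 0 | -5.00 mm | 5% | -5.00 mm | 5% |
| 25% | -3.75 mm | 18% | -4.375 mm | 10% |
| 50% | -2.50 mm | 43% | -3.75 mm | 18% |
| 75% | -1.25 mm | 71% | -3.125 mm | 29% |

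Example, p = 50% and f = 0: (-2.50 + 5)/1.70 - 1.645 = -0.18, and Φ(-0.18) = 0.43.

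**What an estimate in never-trained people could deliver.** With m never-trained per arm, the one-sided half-width is 1.645 × 10 × √(2/m). Power at the same margin, for a true difference of zero, is Φ(5/(10√(2/m)) - 1.645).

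| Never-trained share of 69 | m per arm | Half-width | Power |
|---|---|---|---|
| 75% | 51.75 | 3.2 mm | 82% |
| 50% | 34.5 | 4.0 mm | 67% |
| 25% | 17.25 | 5.6 mm | 43% |

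For the whole sample of 69 per group the half-width is 1.645 × 1.70 = 2.8 mm and power is 90%.

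**The case against.** The strongest reply is that the trial is declared pragmatic and its target is non-healthcare adults as they come. Nothing in the article restricts the target to never-trained people. With -5 mm in the untrained, half the sample previously trained and no difference among them, the true difference in the trial's population is -2.5 mm. That is inside the margin, so declaring noninferiority is correct for that population. This stands. A reader might infer from the table that the trial's type I error is inflated; the article does not support that, because its stated claim concerns the mixed population.

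Three further limits also stand.

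- Previous training means any earlier CPR education, so a yes does not show that the person can already compress to depth. The f = 0 column is the extreme case, which is why f = 0.5 is shown beside it.
- Interim analyses says that subgroup and adjusted analyses are not planned. It does not forbid them. A reader might infer a ban, but later analyses remain open. They would not, however, be prespecified.
- A reader might infer that most volunteers arrive trained. The article expects people interested in CPR to come forward, but interest is not training, and no share is given.

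One might also argue that the margin equals the whole 5 mm gain attributed to conventional training, so that an XR module teaching nothing could pass. Sample size does not say in whom that gain was seen, and it also rests the margin on reduced survival with 5 mm less depth. The point here does not depend on that argument.

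None of this rescues the Recruitment sentence as a statement about interpretation. It deals with balance between arms and is silent on dilution.

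**Conclusion.** The concern holds in a limited form. Admitting previously trained lay adults is a defensible pragmatic choice, and the primary comparison is valid for the mixed sample. What does not hold is the general reassurance that self-selection leaves interpretation unharmed, set beside a plan that makes no use of recorded training history.

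If XR falls short by the full margin in untrained people, the mixed sample would still be declared noninferior with probability 10% to 71% over the scenarios shown with a previously trained share of 25% to 75%. These figures rest on the protocol's SD and sample size, on an assumed share, and on an assumed residual difference among the trained. They measure how far a positive result could mislead about untrained people. They are not error rates for the trial's own hypothesis.

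**What to change.** 1. In Recruitment, qualify the sentence: randomisation protects the comparison from confounding by self-selection, but prior skill in both arms may reduce the difference and so limits what can be concluded about untrained people.
2. In Interim analyses, replace the statement on subgroup and adjusted analyses with two prespecified items:
   - a primary model of mean compression depth adjusted for previous CPR training (yes/no), which adds precision but does not by itself remove the dilution;
   - one supportive estimate of the XR minus conventional difference, with its one-sided 95% limit, by previous training (yes/no).
3. State that the primary conclusion applies to the mixed lay sample, and that no separate noninferiority claim will be made for never-trained people unless that stratum's limit supports it.

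The cost is wording and one extra analysis of an item already collected; eligibility and sample size stay as they are. The downside is imprecision. If half the sample is untrained, the half-width is about 4.0 mm and power about 67%. The stratum's size is also left to chance, because previous training is not a stratification factor. The estimate should therefore be supportive and should not gate the primary result.

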## Assignment of interventions: allocation

### Sequence generation

Participants will be enrolled competitively, but a minimum of 32 participants will be enrolled from each participating institution to minimise racial and physical differences among the participants in each country. Random numbers will be generated with the stratified randomised permuted block design generated in the SAS software (version 9.4; SAS Institute Inc., Cary, NC, USA) by an independent statistician, and the randomisation sequence will be implemented in the Research Electronic Data Capture (REDCap) software (version 9.5.2, Vanderbilt University, Nashville, TN, USA). Institution and sex will be applied as the stratification factors, and REDCap will randomly allocate participants to the XR or conventional group.

### Concealment mechanism

REDCap will use its algorithm for randomisation, which is unknown to the investigators.

### Implementation

Researchers from each institution will enrol participants, and randomisation sequences will be performed with REDCap. After randomisation, the researcher will send the participants to room A (conventional group) and room B (XR group) according to the results of randomisation. Participants will receive corresponding training in each room.

## Data collection and management

### Data management

The answers to the survey questions will be entered directly into REDCap or provided on paper and then entered into REDCap. REDCap is the software toolset and workflow methodology for electronic data collection and management. The person who will enter data for each institution has access only to their institution’s data. If the values that are entered are duplicated or out of range, the Trial Management Group (TMG) will confirm them (Tables 1, 2 and 3). REDCap servers are managed by Seoul National University Bundang Hospital. All web-based information transmission will be encrypted. All protocols, consent forms, and data will be stored in the REDCap system. The collected data will be stored for up to 6 months after the end of the study by the independent data coordinating centre. When it is necessary to store data for a longer period, the data could be sent to the research administration team to be stored for up to 3 years.

### Confidentiality

No personal identifiable information will be stored. Other data will be discarded after this study.

## Statistical methods

### Statistical analysis of the primary and secondary outcomes

Data will be analysed using SPSS 25.0 (IBM SPSS, Inc., Chicago, IL, USA) and Stata 10.0 (Stata Corp, College Station, TX, USA). The primary outcome will be assessed for noninferiority using a 1-sided 95% confidence interval of the mean compression depth between the XR and conventional groups. If the lower limit of the confidence interval is above the prespecified noninferiority limit of − 5, then the noninferiority of XR to conventional training will be established. Continuous variables will be presented as the means ± standard deviations (SDs) or medians with interquartile ranges (IQRs) after the normality of their distributions has been assessed with the Shapiro-Wilk test. The chi-square test or Fisher’s exact test will be used for comparisons of nominal variables, while the independent *t*-test and the Mann-Whitney *U* test will be used to compare continuous variables.

### Interim analyses

There are no planned interim analyses or subgroup or adjusted analyses in the trial.

### Methods for additional analyses

There is a plan to conduct a cost-benefit analysis. In addition, further analysis of the data generated in this trial could be performed in the future. This is stated in the informed consent.

## Oversight and monitoring

### Composition of the coordinating centre and trial steering committee

The Trial Steering Committee will consist of a team at Seoul National University Bundang Hospital and peer reviewers from Children’s Hospital Los Angeles, Royal Manchester Children’s Hospital, and National University of Singapore. TSC will constantly monitor patient safety and data integrity and provide recommendations for the discontinuation of any or all of the study or the modification of any aspect of the protocol. Their roles include the preparation of the protocol and any revisions, the application to obtain approval from the Research Ethics Committee, and the publication of study reports.

Data quality will be monitored by the TMG. It will consist of one investigator at each institution, including two statisticians at Seoul National University Bundang Hospital, who will not be involved in the actual simulation study. If the entered values are duplicated or are out of range, TMG will check and correct the values. Two independent statisticians will be able to access the entire trial dataset, and one investigator from each institution will have access to only their institution’s data.

### Composition of the data monitoring committee, its role, and reporting structure

This study does not need an independent Data Monitoring Committee. We have no plan to perform or publish any interim analyses.

### Adverse event reporting and harms

Any adverse events occurring in the study will be reported to TSC and the IRB. If there is an adverse event that prevents a participant from completing the study, the participant will be withdrawn, and the investigators will provide all necessary support and treatment.

Due to the nature of the simulation study, it does not cause significant harm to participants, and it was reported that VR did not cause significant harm to humans [22–25]. In addition, the study time is as short as 90 min in total. Therefore, no guidelines have been established for the termination of the trial.

